**Fig. 1 Fig1:**
[figure not shown]
Schedule of activities

Six days (± 2) later, participants will be asked to come onsite again for their first dosing day (dosing 1; see Fig. 1). Participants will be given their first single dose of the investigational medicinal product (IMP) and be monitored for 6 h before being discharged. Blood will be drawn prior to drug administration and at 20, 40, 60, 90 120, 180, 240, and 360 min (± 5 min) after administration. Subjective drug effect measures (VAS scales) will also be collected at these time points as per Murphy et al. [17]. EEG measures will be commenced ~ 2 h after administration. Participants will then be discharged with five doses for additional dosing. These doses will be self-administered sublingually two out of every 7 days. Participants will attend a further two re-supply visits during the dosing period. Between days 1 and 57 (dosing period 1; see Fig. 1), they will undertake at-home dosing 2 times a week for a total of 16 doses over 8 weeks.

During this period, they will complete a MADRS on days 14, 28, and 42 (± 3 days) over a video call. Participants will then be asked to come in for their fourth and final visit on day 57 (± 2 days). In this visit, they will undertake a final MADRS, EEG, biomarker panel, and semi-structured interview. If they consent to, at this stage, a whānau (extended family) member will also be asked to attend a separate semi-structured interview considering their whānau member’s experience with the trial (for the full schedule of activities, see Fig. 1). At the discretion of investigators, participants in this trial will have the option to undertake an up to 8-week extension period with the same protocol as the initial part of the trial. Participants will also have three follow-ups, one at 30 days (± 7 days) from the last measure session date and one at 3 months and 6 months from the last measure date.

### Outcomes

The primary and secondary outcome measures of this trial are displayed in Tables 4 and 5, respectively. The primary measures are tolerability and feasibility. Tolerability is measured through the percentage of participants who withdraw from the trial due to adverse events attributable to the treatment regimen where a lower value represents better tolerability. Feasibility will be measured via compliance with the LSDDEP1 protocol, detailed by the percentage of attended clinic visits once enrolled. Both of these measures, alongside participant feedback throughout the trial and in the semi-structured interviews, will allow for the optimisation of procedures for the subsequent LSDDEP2 trial. The full schedule of assessments is detailed in Fig. 1.

**Table 4 Tab4:** Primary measures

Outcome domain	Measure	Definition
Tolerability	Adherence to a regimen of LSD microdoses	Percentage of participants who withdraw from the trial due to adverse events related to the treatment regimen
Feasibility	Compliance with LSDDEP1 study procedures to determine the feasibility of conducting LSDDEP2	Percentage of attended clinic visits once enrolled

**Table 5 Tab5:** Secondary measures

Outcome domain	Measure	Scale
MDD symptoms	MADRS [35] assessed at baseline and at 2, 4, 6, and 8 weeks time points	10 items, each clinician-rated on a 7-point Likert scale, summed to give a total score between 0 and 60
Compliance	Acceptability of trial assessment load	Percentage of assessments completed by assessment type

The participants will also undertake a battery of psychological testing which includes the MADRS which is a secondary outcome in the present study, however, the MADRS will be used as the main efficacy measure for LSDDEP2. The MADRS is one of the most commonly used depression scales in pharmaceutical/regulatory registration trials of depression and consists of 10 items which are summed to a maximum potential score of 60 [36]. Compliance with the trial load will also be quantified as the percentage of assessments completed for each assessment type and time point. This will provide a measure of the acceptability of the trial assessment load, which is important as we do not want to overburden the depressed patient sample. Both the MADRS and compliance will be secondary measures of this trial seen in Table 5.

Safety measures are detailed in Table 6 and include recording of adverse events, measurement of objective safety measures, and checks for serotonin syndrome. Adverse events and their severity will be recorded by the participant in the study app off-site and by the research team on-site. Measures of objective safety will include complete blood count, liver function, renal function, thyroid function, 12-lead ECG, and vital signs at baseline, at the 8-week time point and after completion of the extension period. Echocardiograms will be recorded at baseline and after maximum drug exposure depending on whether a participant enters the extension period. Serotonin syndrome checks will be made on dosing 1 and dosing 2 visits, consisting of checks of body temperature, diaphoresis, shiver/tremor, and agitation and induced clonus if indicated.

**Table 6 Tab6:** Safety measures

Outcome domain	Measure	Scale
Adverse event profile	Assess the incidence of SAEs and AEs by severity, recording in app and on site	Tabulations of AEs by severity and SAE listings from baseline to 1 month post-intervention.
Modification of objective safety measures	Laboratory tests	Complete blood count, liver function, renal function, thyroid function), 12-lead ECG, and vital signs will be measured at baseline and at the 8-week time point and after completion of the extension period. Echocardiogram will be measured at baseline and after the last dose is taken.
Serotonin syndrome	Complete serotonin syndrome checks at each dosing visit	Clonus, diaphoresis, shiver/tremor, and agitation body temperature.

A number of additional exploratory measurements will also be made; for the full description, see Table 7.

**Table 7 Tab7:** Exploratory measures

Outcome domain	Measure	Scale
Anxiety symptoms	HAM-A [37] assessed at baseline and at the 8-week time point.	14 items, clinician-rated on a 4-point Likert scale; these scores combined to give a final composite score.
Depression, stress, and anxiety symptoms	DASS-21 [38], assessed at baseline and at the 8-week time point.	21 items, 5-point Likert scale, from 0 (never) to 4 (almost always). Three subscales reported as summed scores.
Anhedonia symptoms	DARS [39], assessed at baseline and 8-week time point.	4 domains that call for participant examples, rated on a 5-point Likert scale (0–4). Total and each of its four subscales will be compared.
	EEG doors paradigms [40] will be measured at baseline, dosing, and measure time points.	Trials where participants are presented with two doors to select from. In half the trials, they receive feedback indicating monetary gain or loss. Positive ERP ~ 250–300 ms after feedback.
Ruminative symptoms	RRS [41], assessed at baseline and at the 8-week time point	22 items, four scales measuring two aspects of rumination, rated from 1 (almost never) to 4 (almost always).
Quality of life	WHOQOL-BREF [42], assessed at baseline and 8-week time point	26 items, scored on a 5-point Likert scale. Each of its four subscales will be compared.
Connectedness	Watts Connectedness Scale [43], assessed at baseline and 8-week time point.	19 items marked on a visual analogue scale between 0 (“not at all”) and 100 (“entirely”). Each of the three subscales will be compared.
Te Whare Tapa Whā	Hua Oranga [31, 44], assessed at baseline and 8-week time point. Each of its four subscales will be compared.	16 items where each of the constructs is scored by participants on a 5-point scale with descriptors of each provided. Each of its four subscales will be compared.
Daily mood	HAMD-6 self-report [45] will be assessed from baseline daily through until follow-up 1.	6-item scale, clinician-rated. Captures core features of depression.
EEG	The EEG long-term potentiation (LTP) [46, 47], mismatch negativity (MMN) [48], loudness-dependent auditory evoked potential (LDAEP) [49], as well as resting state will be measured at baseline, dosing, and measure time points.	Recorded with 64 channel caps, 5 min eyes-open 5 min eyes-closed resting state, sensory LTP with vertical and horizontal sine gratings on grey background, MMN 5–11 sinusoidal tones, classic oddball response, LDAEP measures serotonergic function, 100-Hz stimulus tones at differing intensities.
Plasma/serum BDNF and mRNA biomarkers	Plasma/serum BDNF samples will be measured baseline. Dosing (pre and 6 h post) and measure time points. Buffy coats will be taken for mRNA samples.	BDNF plasma levels, expression of mRNA markers including proBDNF, BDNF, TrkB, p75NTR, sortilin, 5HT2A, and 5HT1A.
Genotype prediction of outcome measures	Whole blood samples will be taken from participants at baseline.	ValMet66 polymorphism of BDNF gene, SNP analysis related to CYPs and 5HT2A receptor.
Personality trait modification	BFI-2 [50], CFI [51], FFM-Q [52], and MODTAS [53] are measured at screening and measure points.	BFI 60 items on Likert 1–5, for the main personality traits, CFI 20 items from 1–7 giving total score and 2 subscales, FFM-Q 38 items on a 5-point Likert scale, and 34 items on a 5-point Likert scale.
Expectancy	CEQ [54] and short expectancy interview will be measured at baseline and dosing sessions.	6-item scores on a 9-point Likert scale.
Sexual dysfunction	CSFQ-14 [55] will be measured at baseline and measure sessions.	14 items, rated on a 5-point Likert scale.
Sleep, activity, and physiology	Fitness tracker data will be recorded continuously from baseline through to 1 month after completion of regimen.	Wearing of a Garmin activity tracker logging basic measurements including sleep duration, quality, physical activity, heart rate, and stress levels
Daily experience	Daily VAS scales completed every evening in the study app. Participants will be encouraged to record an audio journal in the study app.	HAMD-6 self-report with VAS scales for connected, creativ﻿e, energy, happy, irritable, and jittery. Adverse event reporting.
Withdrawal/discontinuation symptoms	DESS [56] will be measured at the follow-up 1 time point.	Ch﻿eck﻿s for symptoms of discontinuation syndrom﻿e.
Acceptability of study app	Acceptability questionnaire completed every 2 weeks.	5 items considering usability of the app.
Engagement with therapeutic journaling	Journal entries.	Number of journal entries submitted accessed via the app.
Subjective experience	A semi-structured interview.	Conducted with the participant (and whānau member) to record their subjective experiences of being involved in the trial.
Plasma pharmacokinetics	Pharmacokinetic samples will be taken at baseline and 20, 40, 60, 90, 120, 180, 240, and 360 min (± 5 min) after the first dose (dosing).	Quantification by liquid chromatography mass spectrometry
Pharmacodynamics	Pharmacodynamic measurements will be recorded at baseline and at 20, 40, 60, 90, 120, 180, 240, and 360 min (± 5 min) after the first dose (dosing).	Vital signs, speech task, and VAS scales.
Extension period	An intervention extension period is offered to all patients for 8 weeks.	The number of doses administered in this period is the endpoint.
Durability of antidepressant response	MADRS [35] assessments will be conducted at three follow-up time points (1, 3, and 6 months after the final measure session).	10 items, each clinician-rated on a 7-point Likert scale, summed to give a total score between 0 and 60.

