### Dosing protocol

The MDLSD dosing protocol of 10 μg, every third day was intended to closely mirror community microdosing practices, where doses are commonly self-reported as being between 10 and 13 μg [~ 10% of a full dose “trip”; 10, 23] and follow the highly popular Fadiman [10] schedule of dosing every third day. However, LSDDEP1 will consider some of the shortcomings of this scheduling and that of others to modify the dosing schedule to better suit the pragmatic study population’s lifestyle and scheduling considerations. Three key modifications have been made: (1) reduction of the initial dose, (2) dose titration, and (3) reduction of the number of doses a week.

The reduction in the initial dose to 8 µg along with dose titration has been informed by the results of the MDLSD trial [17]. Following the first wave of 19 participants in the MDLSD study, some participants reported feeling over-stimulated. A dose titration procedure was added to the protocol to reduce these unpleasant effects. Over the rest of the MDLSD study, seven participants entered the titration procedure (reduction to 5 μg then increase by 1 μg steps as feasible). Six were in the active intervention group and one in the placebo. Four participants completed the protocol under the titration protocol and three were withdrawn due to adverse events [17]. In the current study, the most appropriate dose for a participant will be the one in which they may feel subtle effects of the LSD, but not to the extent that is negative, overstimulating, or consciousness-altering. Thus, in LSDDEP1, the initial dose has been reduced to 8 μg, increasing at a rate of 1 µg per dose to a maximum dose of 15 µg. If participants experience any uncomfortable effects, their dose will be reduced by 3 µg for their next dose, with this increasing by 1 µg per dose to a level where they are comfortable. The decision to increase/decrease the dose will be based on the participant’s self-report.

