### Drug preparation and administration

Good Manufacturing Practice (GMP) quality LSD Hemitartrate Active Pharmaceutical Ingredient (Psygen Ltd., Calgary, Canada) will be formulated to GMP by Biocell Corp. (Auckland, New Zealand) to produce MB-22001—the investigational medicinal product (IMP) to be used in this trial. Doses are stated as free base equivalents in this document. The contract manufacturer will receive a MedSafe Manufacturing licence for the IMP prior to the commencement of the trial. Investigational products will be labelled consistent with legal requirements. All participants will be offered a lock box to securely keep the IMP at home—and to prevent accidental ingestion by minors or individuals other than the participant. MB-22001 is a liquid formulation that participants can self-administer sublingually.

Participants will be supplied up to a maximum of five LSD doses at a time. The dosing regimen includes 16 doses with the first dose given in clinic on dosing day and subsequent doses self-administered twice a week for 8 weeks The first box of five doses will be supplied at this visit. A further two re-supplies will need to take place over the dosing period. Participants will be asked to dispose of packaging and any residual dose themselves.

Instructions for self-administration will be guided by the study mobile phone application. Doses should be taken no later than 2 pm each day to prevent disruption to sleep. Participants are instructed not to drive or engage in any dangerous activities for a 6 hour window following dosing.

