### Adverse event reporting and harms

An adverse event (AE) is any unexpected medical occurrence (e.g. any unfavourable and unintended sign, including abnormal laboratory or physical exam findings, symptoms, or disease) that arises during participant involvement in the research whether or not they are considered to be related to participation. This definition includes concurrent illnesses, injuries, and exacerbation of pre-existing conditions. It does not include anticipated day-to-day fluctuations of pre-existing disease(s) or condition(s) present or detected at the start of the study that do not worsen. As such, any AE may be temporally or causally associated with the use of the investigational medicinal product.

Adverse events occurring off-site will be recorded via the mobile phone app. Participants will be prompted to describe the event, give a date and time of onset, request a follow-up call from the study team if desired, and give a self-graded severity of the event (mild, moderate, or severe). AEs recorded in the daily report form will be reviewed daily by trial staff. Any AE rated as moderate/severe by a participant will result in an immediate alert to the study team.

Adverse events occurring onsite will be recorded in the case report form (CRF), whether or not they are attributed to trial medication. AEs will be actively sought through non-directive questioning of participants at each study visit. Additionally, patients may voluntarily report adverse events during or between visits, and they can also be identified through physical examination, laboratory tests, or other assessments. AE information recorded in the CRF includes description, date and time of onset, severity grade (mild, moderate, or severe), and the relationship between AE and IMP (related or not related), if the AE is expected or unexpected, action taken and outcome.

All serious adverse events (SAEs) will be reported to MedSafe by the principal investigator as per section 6 of the MedSafe reporting guidelines described in the Regulation of Therapeutic Products in New Zealand Part 11: Clinical trials – regulatory approval and good clinical practice requirements. These are submitted via the HDEC website (https://nz.forms.ethicalreviewmanager.com) as soon as is practical.

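### Within the 8 weeks, the structured serotonin-syndrome check appears to fall only on the first 8 µg dose; no listed item asks about sweating or shivering/tremor at higher home doses

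*Protocol article*

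**What the plan says.** **The check.** The safety part of the Outcomes section lists body temperature, diaphoresis, shiver/tremor, agitation and, if indicated, induced clonus. On timing it says: "Serotonin syndrome checks will be made on dosing 1 and dosing 2 visits". Table 6 agrees: "Complete serotonin syndrome checks at each dosing visit".

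**The doses.** Under Drug preparation and administration: "The dosing regimen includes 16 doses with the first dose given in clinic on dosing day and subsequent doses self-administered". Under Dosing protocol, "the initial dose has been reduced to 8" µg. From there the dose rises by 1 µg each time to a ceiling of 15 µg, and drops by 3 µg after uncomfortable effects.

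**Safety data between clinic visits.** For events off-site, the section on adverse events and harms says of the app: "Participants will be prompted to describe the event", together with onset and self-graded severity. It adds: "AEs recorded in the daily report form will be reviewed daily by trial staff". A moderate or severe rating alerts the team at once. For visits: "AEs will be actively sought through non-directive questioning of participants at each study visit". Table 7 adds: "Daily VAS scales completed every evening in the study app". Those scales include jittery and irritable. The wearable tracker logs heart rate.

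**The concern.** The structured check is tied to supervised dosing, and the supervised dose is the starting dose of a rising schedule. The higher doses are taken at home. There, the listed data collection relies on open description and on two scales that overlap only loosely with tremor and agitation.

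Three features of the trial make this worth raising.

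- Participants may stay on antidepressants other than MAOIs. The protocol suggests that titration might partly offset a dampened response, so co-medicated participants could be among those titrated highest. That last step is an inference, not something the protocol states.
- The team's earlier trial used 10 µg in healthy men, so it does not supply this record for patients at 11 to 15 µg.
- LSDDEP1 exists to pilot procedures for LSDDEP2, which is to use this regimen or one close to it.

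The protocol regards most antidepressants as unlikely to be a safety problem with microdoses. Few events are therefore expected, and the value of this outcome lies mainly in documenting that the signs were looked for and not found. What is at stake is how far up the dose range such a statement can reach.

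**Working it through.** **1. Clinic and home doses.** The plan's own figure reproduces: 2 doses per week × 8 weeks = 16. The supply count agrees: 1 in clinic + 5 taken home + 2 re-supplies × 5 = 16. All 15 later doses are therefore home doses, which leaves no second clinic dose in the 8 weeks.

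**2. Visits.** The Study design section describes in-person screening, baseline, dosing 1 and day 57, and calls day 57 the fourth and final visit. The count reaches four without a second dosing visit (the re-supply visits are evidently not counted), and no dose is described at day 57. The same section labels the 8 weeks dosing period 1, and the extension follows the measure 1 visit under the same protocol. Dosing 2 is thus most plausibly the start of the extension. That is optional, at the investigators' discretion, and at a dose the text does not state.

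**3. Default dose path.** Dose i = min(8 + (i − 1), 15) µg, for i = 1 to 16:

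- 8, 9, 10, 11, 12, 13, 14, then 15 for doses 8 to 16.
- The checked dose is 1 of 16 (6.25%). By amount it is 8 of 77 + 9 × 15 = 212 µg (3.8%).
- The ceiling is 15/8 = 1.875 times the checked dose.

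**4. Paths with a reduction.** Number of the 16 doses above 8 µg:

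| Course | Doses (µg) | Above 8 µg |
|---|---|---|
| Reduced after dose 1, settles at 7 | 8, 5, 6, 7 × 13 | 0 |
| Reduced after 9, settles at 8 | 8, 9, 6, 7, 8 × 12 | 1 |
| Reduced after 10, settles at 8 | 8, 9, 10, 7, 8 × 12 | 2 |
| Reduced after 10, settles at 9 | 8, 9, 10, 7, 8, 9 × 11 | 13 |
| Reduced after 12, settles at 11 | 8 to 12, 9, 10, 11 × 9 | 15 |
| Never reduced | 8 to 14, 15 × 9 | 15 |

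The range is 0 to 15. If a participant has one reduction and then climbs back to 15 µg, 11 to 15 of the 15 home doses exceed 8 µg.

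**5. Table 6 signs set against what is listed for home doses.**

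| Sign | Related item at home |
|---|---|
| Diaphoresis | none listed |
| Shiver/tremor | none direct; jittery overlaps in part |
| Agitation | irritable overlaps in part |
| Temperature, clonus | clinic only |

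**6. Burden of adding items.** The evening form has 6 HAMD-6 items + 6 VAS scales = 12. From baseline to the end of treatment there are about 6 + 56 = 62 evenings, so 12 × 62 = 744 answers.

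- Three added items on 6 + 16 = 22 evenings: 66 answers, and 66/744 = 8.9%.
- Two added items: 44 answers, and 44/744 = 5.9%.

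The daily HAMD-6 continues to follow-up 1, so 744 understates the existing load and both percentages are on the high side.

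**The case against.** **The timing depends on a figure that is not shown.** This stands as a limit. Fig. 1 carries the full schedule and may define dosing 2. A reader might infer that the plan leaves a visit undefined; the document does not support that. If Fig. 1 gave that label to a re-supply visit, the point would weaken, though nothing in the text suggests it and the text still allows only one clinic dose.

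**The article condenses the full protocol.** The app may hold more items than are listed. This stands too, and it is why the point is confined to listed items.

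**Home doses are monitored.** This is correct. A reader might infer that doses above 8 µg go unwatched, or that a blank record means nothing was asked. Neither follows. Low jittery and irritable scores each evening are positive records that partly cover tremor and agitation. Reports are reviewed daily, moderate or severe events raise an alert, events are sought at visits, and uncomfortable effects lower the next dose. What remains uncovered is sweating, with shivering/tremor covered only in part.

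**Self-report cannot replace the clinical check.** This stands. Sweating and tremor are non-specific, and temperature and clonus stay in clinic. A reader might take zero reports in 20 people as bounding serotonin syndrome below 16.8% (1 − 0.025^(1/20)). It would bound only self-reported symptoms, and zero reports of such common symptoms is itself doubtful.

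**Nothing is contradicted.** This is true. The text and Table 6 agree on dosing visits, and checking under supervision is a deliberate choice.

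**Conclusion.** The point holds as a minor, optional improvement and not as an error. On the readable text, the structured check within the 8 weeks sits at 8 µg, while by default all 15 home doses are higher (0 to 15 once reductions are allowed for). A statement that no signs of serotonin syndrome were seen during the regimen would rest on structured data at the starting dose, supplemented by partial and mostly unprompted information above it.

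This rests on two assumptions: that dosing 2 is not a supervised dose within the 8 weeks, and that the app asks nothing beyond what the article lists.

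The documents do not support reading this as evidence that participants are at undue risk. MAOIs are excluded and few events are expected. Tolerability and feasibility, the primary outcomes, are unaffected.

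**What to change.** No visit needs to be added.

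1. Add yes/no items for unusual sweating and for shivering or tremor to the existing evening app form, on the 16 dosing evenings and on the roughly 6 evenings between baseline and dosing 1. The pre-dose evenings allow background signs, such as those from an antidepressant, to be separated within person. An agitation item is optional, given the irritable scale. A lighter alternative is to ask the items at the existing day 14, 28 and 42 video calls (2 or 3 items × 3 calls = 6 to 9 answers), at the price of longer recall and a weaker link to the dose taken.
2. Handle a yes through the daily review already in place. Keep the immediate alert for moderate or severe ratings, or for more than one sign.
3. Tabulate the answers by dose taken and by antidepressant use, separately from spontaneously reported adverse events, and label them as self-reported signs and not as a rate of serotonin syndrome.
4. Report the dosing 1 result as a first-dose (8 µg) check.

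**Cost.** The change means a form edit and 44 to 66 extra answers per participant, in a trial that aims to limit burden. Some positives will be non-specific. Prompting may influence titration, which is driven by self-report. Recruitment opened on 19 July 2023, so participants already enrolled would contribute mixed data, and those past baseline would lack the pre-dose evenings.

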### Safety of LSD microdosing

The trend for patients with psychological symptoms to self-medicate with psychedelic microdoses is both interesting and concerning. Although many studies indicate that LSD is relatively safe in terms of physical effects [17–21], the safety of microdosing in specific groups with mental health conditions is unknown.

Safety data from healthy volunteers is available from laboratory-based randomised controlled trials. In four papers with relatively minimal safety reporting, LSD microdoses were administered to approximately 138 participants in total [19–22] with no serious adverse events reported in these studies. Three of these studies have shown dose-dependent increases in blood pressure [19, 20, 22]. In a more thorough documentation of adverse effects, Family et al. [18] reported treatment-emergent adverse events (TEAEs) in 48 healthy older volunteers receiving six doses, one every 3 days, of either 0, 5, 10, or 20 μg of LSD. Although between 66.7 and 83.3% of participants in each group reported TEAEs, the only statistically significant difference between the groups was the frequency of headaches. The percentage of volunteers at LSD doses 5 μg, 10 μg, and 20 μg reporting headaches were 16.7%, 50.0%, and 25.0%, respectively, compared to 8.3% in the placebo group. All headaches were either mild or moderate. No change in vital signs was observed [18].

The phase 1 healthy volunteer (MDLSD) study we recently conducted using home administration of LSD microdoses similarly reported no serious or severe adverse events [17]. Adverse events included mild nausea, potential increases in jitteriness, stress, vivid dreams, and anxiety, but the increase in headache frequency reported by Family et al. [18] was not replicated in the MDLSD study—which had a much larger sample size. No changes in vital signs were detected.

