The screening process will be split into two sessions, the first of which will occur remotely over phone/video call for participant convenience. This will involve obtaining medical and psychiatric history, carrying out the MADRS and C-SSRS and assessment of inclusion/exclusion criteria (see Tables 1 and 2). Both the MADRS and C-SSRS have been endorsed for remote use [34]. At this stage, the research team will ensure that the participant knows the time requirements, risks, and assessments required for the trial and informed consent will be confirmed via their verbal understanding of the information presented and through written, e-signed informed consent. Verbal consent and eligibility will be confirmed at each session. If eligible, participants will be invited to an in-person screening. This will occur onsite and include physical measurement of height, weight, vital signs, 12-lead ECG, laboratory tests, drug/alcohol breathalyser test, and pregnancy test.

If participants are eligible after the screening battery, they will be invited to attend a baseline session onsite (baseline visit; see Fig. 1). This will involve baseline electroencephalography (EEG) readings, MADRS and other depression inventories, and providing blood samples for the biomarker panel. At this stage, participants will be given a wearable activity tracking and a study mobile phone app will be installed on their phone. If a participant does not have a mobile phone, one will be provided for them. At this stage, adverse event (AE) recording, sleep and activity tracking, and daily questionnaires will commence. Echocardiograms will also be measured at a subcontracted clinical facility.

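### Table 6 tabulates adverse events over one span that opens about six days before the first dose; splitting it by period is a minor, cheap improvement

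*Protocol article*

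**What the plan says.** The safety table in the Outcomes section (Table 6) states the AE output as "Tabulations of AEs by severity and SAE listings from baseline to 1 month post-intervention". Severity is the only breakdown named, and one span is given.

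The Study design section fixes where that span opens. At the baseline visit, "At this stage, adverse event (AE) recording, sleep and activity tracking, and daily questionnaires will commence". It then says that, six days (± 2) "later, participants will be asked to come onsite again for their first dosing day". Drug exposure starts at that second visit.

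The section on adverse event reporting and harms defines an AE as an unexpected medical occurrence that "arises during participant involvement in the research whether or not they are considered to be related to participation". The definition is not tied to dosing.

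The same section describes what is captured. For off-site events entered in the app, "Participants will be prompted to describe the event, give a date and time of onset". For events entered in the case report form, onset date and time are recorded, and also "the relationship between AE and IMP (related or not related"). Relatedness is not listed among the app prompts.

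**The concern.** Every participant receives LSD, so no placebo group shows how many events would have occurred without it. The AE table therefore has to separate exposed from unexposed time by itself. As stated it does not. An event on the second day after the baseline visit, before any drug, enters the same severity count as an event on a dosing day, in the extension or three weeks after the last dose.

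The trial exists to prepare LSDDEP2. A reader planning that trial would want to know which events began under treatment, and a single count over the whole span cannot say. The pre-dose days could also serve as a modest within-person reference, but only if they are shown on their own.

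**Working it through.** The plan gives no AE count or rate to reproduce, so the check is of the span itself.

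**Inputs (Study design and Extension period sections)**
- Baseline visit to first dose: 6 days, range 4 to 8.
- First dose on day 1 to final visit on day 57 (± 2): 56 days, range 54 to 58.
- First follow-up: 30 days after the last measure session, range 23 to 37. This is taken as the one month after the intervention in Table 6.
- Optional extension: up to 8 weeks (56 days), starting up to 14 days late.
- Sample size: 20.

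**Does the span really open before dosing?** The pharmacokinetic row of Table 7 uses the word baseline for the pre-dose sample on the first dosing day. If Table 6 meant that, there would be no pre-dose gap. But Study design ties the start of AE recording to the separate baseline visit, so for AEs the earlier date applies.

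**Pre-dose share of a participant's span** = gap ÷ (gap + dosing period + follow-up)
- Nominal: 6 ÷ (6 + 56 + 30) = 6 ÷ 92 = 6.5%.
- Smallest: 4 ÷ (4 + 58 + 37) = 4 ÷ 99 = 4.0%.
- Largest: 8 ÷ (8 + 54 + 23) = 8 ÷ 85 = 9.4%.
- With a full extension: 6 ÷ (92 + 56) = 6 ÷ 148 = 4.1%.
- With a full extension and a 14-day delay: 6 ÷ 162 = 3.7%.

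**Participant-days for 20 completers without extension, nominal timing**

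| Period | Days each | Participant-days | Share |
|---|---|---|---|
| Pre-dose | 6 | 120 | 6.5% |
| Dosing period | 56 | 1,120 | 60.9% |
| Follow-up | 30 | 600 | 32.6% |
| Total | 92 | 1,840 | 100% |

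**Effect of starting the on-treatment count at the first dose:** the span from first dose to first follow-up is 92 − 6 = 86 days.

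**Can the split be made from data already planned?** Onset date and time are recorded for both off-site and on-site events, and the first dose is given in clinic. Placing each event before or after the first dose therefore needs nothing new. A split by relatedness is certain only for events that reach the case report form.

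**The case against.** The strongest reply is that period splits, a treatment-emergent definition and tables by relatedness normally belong in a SAP, which is not at hand. Table 6 does not forbid finer tables, and SAE listings can show onset. That stands as far as it goes: the absence of a treatment-emergent definition is not the point here. What remains is that the article does state a window and a breakdown, and the stated window includes unexposed time.

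A second reply is that the pre-dose stretch is short and the primary measure is untouched. Both are correct, and they make this a minor point.

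A reader might draw stronger conclusions that the documents do not support:

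- **That 39% of the span is misplaced.** Pre-dose and follow-up time together are (120 + 600) ÷ 1,840 = 39.1%, but 600 of those 720 participant-days are post-treatment follow-up, which a safety window should cover. Only the pre-dose part is out of place in an on-treatment count.
- **That the number of pre-dose events can be projected.** The section on the safety of LSD microdosing describes an earlier placebo-controlled study "in 48 healthy older volunteers receiving six doses, one every 3 days, of either 0, 5, 10, or 20" μg, and adds: "Although between 66.7 and 83.3% of participants in each group reported TEAEs". That range spans four groups, three of them on active LSD. The text does not say which value belongs to placebo and gives no observation period. It is not a background rate for this trial.
- **That comparing dose days with other days would isolate a drug effect.** Participants choose dose days partly around events and driving, know they have taken the drug, and plan an activity. Detection also differs: the first dose is monitored for 6 hours in clinic, and home dose days bring app prompts and evening journaling. Any of these could raise the recorded rate without a drug effect. Nor is this the only within-person comparison available, since the periods before, during and after dosing are in the same people.

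**Conclusion.** The point holds as a minor improvement to a stated output. Taken literally, Table 6 mixes events before any exposure with those during and after treatment, in a single-arm trial. Pre-dose time is about 6.5% of a 92-day span (4% to 9% across the visit windows) and about 4% with a full extension.

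These shares assume completers who attend within the visit windows, and that the AE span opens at the baseline visit and closes at the first follow-up. They are shares of time, not of events; how many events fall before the first dose is unknown. The tolerability outcome, which counts withdrawals due to AEs attributable to the regimen, does not change.

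**What to change.** Amend the AE row of Table 6 as follows:

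1. Tabulate AEs by severity, and by relatedness where it is recorded, separately for pre-dose (baseline visit to first dose), dosing period, extension and follow-up. Give participant-days for each period.
2. Assign events by recorded onset date and time. Count none with onset before the first dose as on-treatment.
3. State which period holds the delay of up to 14 days before an extension.
4. Keep the SAE listings as they are.

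Optionally, and as an exploratory item only, report descriptively the AE rate on dose days against other days of the dosing period. State beside it that dose days differ in expectancy, chosen timing, activities and AE ascertainment, so a difference is not a pure drug effect.

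The cost is one table row and a small amount of descriptive tabulation, which fits the descriptive approach in the statistical analyses section. The period split needs no new data. The downside is sparse cells when 20 participants are divided by period, severity and relatedness.
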